**Discussion:**

This trial may not only provide evidence on the efficacy of a 5% lidocaine patch for acute postoperative pain management after unilateral inguinal hernia repair, but also demonstrate the efficacy and safety of the patch for post-discharge pain management.

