## Methods/design

### Study design

This is a single-center, prospective, superiority, double-blind, randomized, controlled clinical trial. This study has been approved by the Institutional Review Board (B-2007-625-006) of Seoul National University Bundang Hospital. Written informed consent to participate will be obtained by the principal investigator at the time of screening for eligibility on the patient’s initial visit to outpatient clinic. After surgery, the experimental group will receive 5% lidocaine patches (Lidotop Cataplasma; SK chemical Co. Ltd, Seongnam, Korea), and the control group will receive placebo patches that were specially made for this study. The comparator is a well-made placebo patch to evaluate not only the efficacy but also the safety of the 5% lidocaine patch. The overview of the study design is shown in Fig. 1.

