### Inclusion and exclusion criteria

The inclusion criteria are (a) age between 19 and 80 years, (b) American Society of Anesthesiologists risk classification score of I (healthy) or II (mild systemic disease), (c) elective open surgery for unilateral inguinal hernia, and (d) admission to and discharge from the day surgery unit on the day of the surgery itself.

The exclusion criteria are (a) obesity (body mass index > 30 kg/m^2^), (b) renal insufficiency (serum creatinine level ≥ 1.4 mg/dL), (c) liver insufficiency (serum aspartate transferase level ≥ 120 IU/L or serum alanine transaminase level ≥ 120 IU/L), (d) known hypersensitivity to amide-based local anesthetics, (e) use of class I antiarrhythmic medication such as tocainide and mexiletine, and (f) refusal to participate.

The principal investigator of this study will not exclude patients who are likely to participate in this study based on race or socioeconomic status. Every effort will be made to ensure that as many patients as possible who meet the inclusion criteria will be included. Patients will be informed of the purpose of the study so that they can represent the entire population of patients undergoing general anesthesia.

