### Sample size calculation

The sample size for the primary outcome (VAS score at the time of discharge) was determined based on a previous study on patients with ventral hernia that compared the VAS scores of a control group (4.8 ± 1.4) with those of a lidocaine patch group (3.1 ± 1.6) and observed a difference of 1.7 [9]. For a one-sided analysis with a type I error (α) of 5% and a power (1-β) of 0.8, the number of participants required per group is 14. Anticipating a dropout rate of 10%, the number of participants required per group is 16, resulting in a total sample size of 32.

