### Randomization

We will randomize the participants in a 1:1 ratio to the lidocaine patch group or the placebo patch group. We will achieve block randomization using Random Allocation Software (Isfahan University of Medical Sciences, Isfahan, Iran). A research nurse from the anesthesiology department who is not involved in the study will generate the randomized allocation sequence and deliver the allocated patches. The patches will be given directly to the anesthesiologist and surgeon responsible for applying it at the end of the surgery. The participants and researchers (the anesthesiologist and surgeon) who evaluate the patients’ clinical parameters will be blinded to the group allocation.

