**Fig. 2 Fig2:**
[figure not shown]
Location of the patch. Irrespective of the type of patch used (5% lidocaine or placebo), one patch will be applied 1 cm above and another 1 cm below the surgical wound

Before discharge from the day surgery unit, we will allow participants to use additional pain medications such as opioids or non-steroidal anti-inflammatory drugs as needed during their recovery from the general anesthesia. Either fentanyl (50 μg; Hana fentanyl citrate, Hana Pharm. Co., Ltd, Seoul, Korea) or ketorolac (30 mg; Trolac, Whan In Pharm. Co., Ltd, Seoul, Korea) will be prescribed. Fentanyl will be prescribed a maximum of three times when a patient experiences pain with a VAS score of > 5. Ketorolac will be prescribed if a patient experiences any adverse effects following fentanyl administration. Oral medications such as tramadol/acetaminophen (37mg/325 mg; Rapicet, Chong Kun Dang Pharm. Co., Seoul, Korea) will be prescribed to each patient at the time of discharge for pain management. However, additional pain medication or interventions outside of the protocol during the study period, which is from the surgery to 1 week after surgery, are prohibited.

This study protocol includes criteria for discontinuing intervention. If a participant withdraws their consent, decides to undergo extra surgery besides the unilateral inguinal hernia repair after random allocation, or if any adverse effects with local anesthetics are shown, they will discontinue the study.

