Through these studies, which included randomized clinical trials and meta-analyses, the safety and efficacy of using a 5% lidocaine patch for acute postoperative pain management has been established. However, most of these studies were on patients who received hospital care and patient-controlled analgesia following surgery, in which the patients’ acute pain was rapidly treated by medical staff. However, the lidocaine patch has advantages comparing with other operative pain managements, such as abdominal muscle fascia and peritoneal nerve block and patient-controlled analgesia. It is non-invasive and simple to apply since the lidocaine patch may produce an analgesic effect without a complete sensory blockage by penetrating skin depth of only 8 to 10 mm [15]. The lidocaine patch may also have a great safety profile for application in an outpatient clinical setting for acute postoperative pain.

We have designed this clinical trial to investigate the efficacy of a 5% lidocaine patch for postoperative pain management without additional medical attention. Therefore, we will enroll patients undergoing open unilateral inguinal hernia repair at a day surgery unit. We believe that in addition to demonstrating the efficacy of a 5% lidocaine patch on acute postoperative pain after unilateral inguinal hernia repair, we will be able to provide evidence on its efficacy and safety for post-discharge pain management. In summary, we hypothesize that a 5% lidocaine patch is an effective option for acute postoperative pain management following unilateral inguinal hernia repair, and it can be safely used in an outpatient clinical setting.

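### The stopping rule announces an end to the intervention but, as written, takes participants with a local-anaesthetic adverse effect out of the study and its remaining assessments

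*Protocol article*

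**What the plan says.** The rule stands in Methods/design, Procedure, in the paragraph after the rescue-medication text. Its opening sentence reads "This study protocol includes criteria for discontinuing intervention". The next sentence names three triggers: withdrawn consent, a decision after allocation to have additional surgery, and a local-anaesthetic adverse effect. All three have the same consequence; for the last the text is "if any adverse effects with local anesthetics are shown, they will discontinue the study". No severity threshold is set. The same section defines the study period as running from surgery to 1 week afterwards.

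The Outcomes section schedules VAS at discharge (primary, about 2 to 3 h after surgery), at 24 h and at 1 week. Complication rates and the total of oral analgesics are collected at the 1-week visit.

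Safety is a declared aim in three places. Study design says the placebo was chosen "to evaluate not only the efficacy but also the safety of the 5% lidocaine patch". The abstract expects the trial to "demonstrate the efficacy and safety of the patch for post-discharge pain management", and the Discussion says "we will be able to provide evidence on its efficacy and safety for post-discharge pain management".

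**The concern.** Stopping a patch and leaving a trial are different actions. The lead-in sentence describes the first and the rule itself prescribes the second. An adverse effect is thereby treated like withdrawn consent, although only withdrawn consent requires follow-up to end.

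If staff apply the rule as written, the patients who reacted to the product under test have no 1-week safety record. The loss may also be related to treatment. Assessors are blinded, so suspected reactions trigger exit in both arms, but genuine effects of lidocaine from the patch can occur only in the active arm. The direction of any resulting bias cannot be stated.

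**Working it through.** **Text check.** The article gives no figure on this point to reproduce, so the first step is to set the relevant sections side by side.

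- Procedure, lead-in: the criteria concern the intervention.
- Procedure, rule: the participant leaves the study, which lasts to 1 week.
- Strategies for study retention: visit reminders go to all participants until the study period ends. This leans towards continued follow-up, but does not mention participants who have been discontinued.
- Data monitoring: adverse drug reactions are reported. The triggering event is therefore captured; the later scheduled assessments are not.
- Inclusion and exclusion criteria: patients with "known hypersensitivity to amide-based local anesthetics" and users of class I antiarrhythmics are excluded, which should lower the event rate.

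No section says that a participant stopped for an adverse effect continues in follow-up.

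**Inputs for size.** From Sample size calculation: n = 16 per arm, SDs 1.4 (control) and 1.6 (lidocaine), difference 1.7, one-sided α 0.05. Assumed, because the article gives neither: event rate r = 1%, 2% or 5%; VAS difference between lost and retained patients d = 1 to 3 points.

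**Chance of losing patients from one arm.** P(at least one) = 1 − (1 − r)^16. P(two or more) = P(at least one) − 16r(1 − r)^15. Expected shift in the arm mean = r × d.

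| r | At least one | Two or more | Expected shift (d = 1 to 3) |
|---|---|---|---|
| 1% | 1 − 0.851 = 0.149 | 0.149 − 0.138 = 0.011 | 0.01 to 0.03 |
| 2% | 1 − 0.724 = 0.276 | 0.276 − 0.236 = 0.040 | 0.02 to 0.06 |
| 5% | 1 − 0.440 = 0.560 | 0.560 − 0.371 = 0.189 | 0.05 to 0.15 |

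**Effect of one actual loss.**

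- Safety denominator: 1/16 = 6.3% of the arm.
- Shift in the arm mean: d/16 = 1/16 to 3/16 = 0.0625 to 0.1875 VAS points.
- Standard error of the difference: √((1.4² + 1.6²)/16) = √(4.52/16) = 0.53, if the planning SDs also hold at the later visits.
- Ratio: 0.0625/0.53 = 0.12 and 0.1875/0.53 = 0.35 standard errors.

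**Power for the primary outcome** (noncentral t, one-sided α 0.05, difference 1.7, SDs 1.4 and 1.6, control versus lidocaine):

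- 16 versus 16: 0.931
- 16 versus 15: 0.922
- 16 versus 14: 0.912

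**The case against.** The strongest reply is that this is loose wording. The lead-in speaks of the intervention, so the word for study may simply mean study treatment, and reminders to all participants fit that reading. The article also condenses a fuller protocol that may settle the matter. Both points are fair, and they make the text ambiguous rather than certainly harmful. But the article states the exit rule itself and nowhere corrects it, so this is more than a detail left out, and staff could follow either reading.

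The exposure is also narrow. The patches go on once, at the end of surgery, and their effect has worn off by the first-day visit, so reactions should cluster early. That visit has a clinical purpose, wound dressing, so patients would probably attend anyway. The triggering event is reported. The 24 h VAS bears less on efficacy, and the primary VAS is touched only by events in the 2 to 3 h before discharge. All of this stands and limits the size of the problem. It does not restore the 1-week complication record or analgesic total.

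Suspected reactions in placebo patients would trigger exit too, since those "who evaluate the patients’ clinical parameters will be blinded to the group allocation". An imbalance between arms is therefore possible but not shown.

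Finally, the plan allows for dropout: "Anticipating a dropout rate of 10%, the number of participants required per group is 16". That protects the number of participants. It does not deal with loss that may depend on treatment.

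**Conclusion.** The concern holds. The announced scope and the prescribed action differ, and the literal rule discards follow-up on the patients who matter most for a stated aim. The consequence is probably small and falls mainly on the secondary and safety comparisons; the primary test is hardly affected.

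The size rests on assumed event rates and VAS differences, and on planning SDs taken from a ventral hernia study being applied to later visits. The true event rate is unknown. The change is worth making because the rule is operative, the arms are small and the remedy is nearly free. Confidence is medium, since the looser reading may be what was intended.

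**What to change.** Reword the rule in Procedure along these lines: a local-anaesthetic adverse effect stops or removes the patches; the participant continues with the discharge, 24 h and 1-week assessments, is kept in the randomised arm, and has the event counted by arm in the safety results. Withdrawal of consent ends follow-up. After additional surgery, continued safety follow-up is reasonable; how those pain scores are used is a separate analysis choice. The decision on when to stop the patch is not questioned.

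The cost is a change of wording, made through a protocol amendment. No visits are added, because the assessments and reminders are already planned. Trial status predicted completion in October 2021 and the article appeared in September 2022. If that schedule held, what remains is to report, by arm, how many participants left under this rule, when, and which assessments they missed.

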### Outcomes

The primary outcome is pain intensity measured using the VAS at the time of discharge from the day surgery unit, which is approximately 2 or 3 h after the surgery. We will evaluate each patient’s VAS scores in three situations: at rest, when coughing, and when moving. The secondary outcomes are pain intensity at 24 h and 1 week after surgery. We will evaluate each patient’s VAS score when they visit the clinic for wound dressing on the first postoperative day when the pain-relieving effect of the patch has been worn off. At the follow-up visit 1 week after surgery, we will assess the VAS score, the rates of postoperative complications (such as nausea, vomiting, and desaturation), and the total amount of oral combination analgesics used after discharge. To understand the correlation with general anesthesia and lidocaine patch, we will additionally analyze the amount of intraoperative opioid use, time to recovery, and pain intensity at 30 min after surgery as a part of the secondary outcomes. The participants’ demographic characteristics, such as age, sex, body weight, and height, will also be recorded.

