### Hypothesis

Evaluating the efficacy of a 5% lidocaine patch on acute postoperative pain in a patient undergoing unilateral inguinal hernia repair at a day surgery unit is the main purpose of this study. This prospective, superiority, double-blind, randomized, controlled clinical trial was designed based on the hypothesis that patients who applied the lidocaine patch will have a lower VAS score at discharge after surgery than patients who applied the placebo patch after unilateral inguinal hernia repair at a day surgery unit.

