### Data analysis

All statistical analyses will be performed using Statistical Package for the Social Sciences version 25.0 for Windows (IBM, Armonk, NY). The participants’ demographic characteristics will be analyzed using descriptive statistics. After verifying the normality, the Student t-test or Mann–Whitney *U* test will be used to analyze the numerical data. For categorical data, we will use the chi-squared test or Fisher’s exact test. All results with a p-value of less than 0.05 will be considered as significant.

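### The primary VAS score at discharge is not fully identified: pain is scored at rest, coughing and moving, and no rule says which score decides the trial

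*Protocol article*

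**What the plan says.** Outcomes, in the protocol article, defines the endpoint as a single quantity: "The primary outcome is pain intensity measured using the VAS at the time of discharge from the day surgery unit". The next sentence says that the trial will evaluate "VAS scores in three situations: at rest, when coughing, and when moving". No section says which of these is primary, how they would be combined, or how many must favour the patch.

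Elsewhere the endpoint is one number. The Hypothesis section expects that lidocaine patients "will have a lower VAS score at discharge after surgery than patients who applied the placebo patch". The abstract and Sample size calculation likewise refer to one VAS score at discharge and name no situation. The planning values are 4.8 ± 1.4 (control) and 3.1 ± 1.6 (lidocaine), a difference of 1.7. The calculation is described as one-sided, with "type I error (α) of 5% and a power (1-β) of 0.8", and arrives at 14 per group, or 16 after 10% dropout.

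Data analysis compares the groups on numerical data with "the Student t-test or Mann–Whitney" *U* tests, one variable at a time, and closes with: "All results with a p-value of less than 0.05 will be considered as significant". It does not say whether the tests are one- or two-sided.

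**The concern.** Pain at rest, on coughing and on moving are three different measurements, and a patch could appear to work on one and not on another. The hypothesis and the sample size each need one defined variable, and the text supplies three candidates.

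Two things are at stake. First, the variable that was sized is unknown: the planning scores are not tied to any situation, so nobody can tell whether 14 per group suits the score eventually called primary. Second, the primary score could be settled after the results are known. The blanket threshold in Data analysis sets no order among the three scores and so does not close that door. In a 32-patient superiority trial, a reader could not then tell a pre-specified result from a selected one.

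**Working it through.** **1. The plan's own sample size.** Inputs are from Sample size calculation: difference 1.7, SDs 1.4 and 1.6, α 0.05, power 0.80.

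- Pooled SD = √[(1.4² + 1.6²)/2] = √2.26 = 1.503.
- Standardised difference = 1.7/1.503 = 1.131, squared 1.279.
- Normal approximation, n per group = 2(z_α + z_β)²/1.279.
  - Two-sided: 2(1.960 + 0.842)²/1.279 = 12.3, so 13.
  - One-sided: 2(1.645 + 0.842)²/1.279 = 9.7, so 10.
- Noncentral t calculation:
  - Two-sided: 14 per group (power 82.1%).
  - One-sided: 11 per group (power 82.0%).
- Dropout: 14/0.90 = 15.6, so 16 per group and 32 in total.

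The stated 14 is reproduced by a two-sided 5% t-test. It is not reproduced by the one-sided test that the section describes, for which 11 would do.

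**2. Error rate if any one of the three scores could support the claim.** The correlation between the scores is not given, so it is an assumption, varied from 0 to 0.9. With independent scores:

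- At least one p < 0.05: 1 − 0.95³ = 14.3%.
- At least one two-sided p < 0.05 in favour of lidocaine: 1 − 0.975³ = 7.3%.

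For correlated scores, three equally correlated normal outcomes were simulated under no effect, with 14 per group, t-tests and 200,000 runs:

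| Assumed correlation | Any of three, two-sided 5% | Any of three, two-sided 5%, favouring lidocaine | Any of three, one-sided 5% | All three, two-sided 5% |
|---|---|---|---|---|
| 0 | 14.1% | 7.3% | 14.3% | 0.01% |
| 0.3 | 13.5% | 6.7% | 12.9% | 0.1% |
| 0.5 | 12.7% | 6.3% | 11.9% | 0.3% |
| 0.7 | 11.0% | 5.5% | 10.3% | 0.8% |
| 0.8 | 10.0% | 5.0% | 9.3% | 1.3% |
| 0.9 | 8.4% | 4.3% | 8.0% | 2.1% |
| Nominal | 5% | 2.5% | 5% | 5% |

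The difference between 14.1% and 14.3% in the first row is simulation error.

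**3. What each remedy costs in patients.**

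- One named situation: the error rate returns to nominal, and 14 per group (16 with dropout) stands.
- Three co-equal scores with Bonferroni, α = 0.05/3 = 0.0167, two-sided: 18 per group by the t calculation. Then 18/0.90 = 20 per group, 40 in total. With 14 per group, power for each score falls from 82% to 67%.

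**The case against.** The strongest reply is that the article names one primary outcome, and the sentence on three situations only describes how pain is measured. A reader might infer that the three scores are co-primary, that each is tested for success, and that the trial therefore has three chances to win. The documents do not support that. No sentence makes the scores co-primary or says that any one suffices, and the p-value sentence is a general threshold, not a success rule. If all three had to be significant, the error rate would be below nominal at every correlation tried. If one had been chosen in advance, it would be exactly nominal. This stands, so the inflation is conditional.

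The direction of error also matters. The hypothesis is that lidocaine lowers pain, and the two-sided 8% to 14% includes false results favouring placebo. Counting only results that favour lidocaine, the figure is about 4% to 7%. That exceeds the 2.5% per direction of a two-sided test, but set against the one-sided 5% that the sample size declares, the excess is small or absent at high correlation. If the tests are themselves one-sided at 5%, the 8% to 14% range applies again. The uncorrelated figure is an upper one, because the scores come from the same patient at the same time.

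It can also be said that multiplicity rules and the handling of secondary outcomes are often left to a full protocol or analysis plan, which are not shown. That is fair for the secondary outcomes, and they are no part of this point. It does not excuse the primary variable, on which the hypothesis and the sample size in this document depend.

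**Conclusion.** The point holds as a badly fixed primary endpoint. Discharge VAS is treated as one score and measured as three, with no primary situation, combining rule or success rule, under a significance rule that covers all results. The choice is therefore open until the data are seen.

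The size depends on how that choice is made. It is about 8% to 12.7% instead of 5% if any one score could carry the claim (correlations 0.9 to 0.5; 14% at most). It is about 4% to 6% instead of 2.5% for two-sided results favouring lidocaine (7% at most), and there is no inflation if all three are required. These figures assume normal scores, equal correlations and 14 evaluable patients per group. The documents do not establish that the 5% level is broken; they leave it unprotected.

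The unclear sidedness is part of the same gap, because the nominal level cannot be stated until the one-sided label and the figure of 14 per group are reconciled.

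**What to change.** - **Outcomes:** before unblinding, name one situation at discharge as the sole primary outcome. It should preferably be the one that the 4.8 and 3.1 planning scores refer to. If that cannot be established, the investigators should choose one and justify it; the document gives no ground for preferring any of the three. Report the other two as secondary, or test them in a stated fixed order, stopping at the first non-significant result.
- **Hypothesis and Sample size calculation:** name the same situation.
- **Data analysis:** limit the confirmatory meaning of p < 0.05 to that outcome and any stated sequence, and give the sidedness of the test. Make it agree with Sample size calculation, where 14 per group fits a two-sided 5% test (power 82%), while 11 would suffice for the one-sided test described.
- **Timing:** Trial status gives recruitment from March 2021 and predicted completion in October 2021, so the choice should be dated. If data have already been seen, report all three scores and state that the primary situation was not fixed in advance.

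The cost is wording, provided that it is done before unblinding; no patients are added. The sponsor gives up the option of claiming success on whichever situation turns out significant.
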